### Weight-adjusted effective volume of 0.5% ropivacaine for costoclavicular-cervical plexus blocks undergoing arthroscopic shoulder surgery: a dose-finding study

#### INTRODUCTION:

Rotator cuff injuries are very common clinically, especially in older patients.[1] Presently, Shoulder arthroscopic rotator cuff repair is becoming more and more widely used in clinical practice.[2] Interscalene brachial plexus block（ISB）It is a classic technique to control pain after shoulder surgery. Compared with general anaesthesia alone, it can significantly shorten the length of hospital stay and reduce postoperative pain scores.[3] However, the rate of septal nerve block is high.[4]

Recent It has been found that costoclavicular space combined with cervical plexus block (CCB-CPBs) can also produce similar analgesic effects as ISB in shoulder arthroscopic surgery. In addition, CCB-CPBs have a lower incidence of HDP than ISB, so it may be a safer form of analgesia.[5,6] Subsequently, an autopsy study found that CCB could block the axillary nerve and suprascapular nerve, which are the main nerve branches innervating sensation in the shoulder joint. [7]

Thus, current evidence suggests that CCB-CPBs can provide postoperative analgesia for shoulder arthroscopic surgery, however, excessive local anesthetic volume may still cause HDP [8]; A small local anesthetic volume may cause inadequate analgesia. Therefore, exploring the optimal dose of CCB-CPBs to provide a perfect postoperative analgesic effect while avoiding HDP is an urgent clinical problem.

#### OBJECTIVE

This study explored the optimal dose of ropivacaine for analgesia after shoulder arthroscopic surgery by determining the 50% effective dose (ED50) and 95% effective dose (ED95) of ropivacaine required for postoperative analgesia after shoulder arthroscopic surgery by CCB-CPBs for analgesia after general anesthesia for shoulder arthroscopic surgery.

#### METHODS

##### Subjects

This study plans to include 40 patients who underwent shoulder arthroscopic surgery under anesthesia under general anesthesia combined with CCB-CPBs.

##### Inclusion Criteria

American College of Anesthesiologists (ASA) Class I~II

Age 18~75 years old

The body mass index is 18~30kg/m^2^

##### Exclusion Criteria:

Allergy to amide local anesthetics

Nerve damage or paresthesias in the affected limb

History of subclavian fossa surgery

Have bleeding tendencies or coagulopathy

Infection at the puncture site

Mental, speech, or hearing impairments

##### Study Protocol

No premedication will be given to the patients, and they will be asked to observe an eight-hour fasting period. Once they enter the operating room, we will establish a peripheral intravenous access in the non-operative upper limb using a 16-gauge catheter for fluid administration. A rapid peripheral intravenous preload using Ringer's lactate solution will be commenced at a rate of 10 ml/kg, and this rate will be sustained throughout the entire procedure. Standard non-invasive monitoring methodologies, including non-invasive blood pressure measurement, pulse oximetry, and electrocardiography, will be implemented.

###### Baseline diaphragmatic excursion measurement

The patient will be positioned in a semi-sitting position with the head raised approximately 30 degrees. Via the anterior subcostal route, either the liver or the spleen will serve as an acoustic window. The excursion of the hemidiaphragm will be measured by utilizing the M-mode which will be equipped with a low-frequency (1 to 5 MHz) ultrasound probe. Stable waveforms will be documented during deep breathing, and the corresponding values will be recorded.

###### Ultrasound-guided costoclavicular space combined with cervical plexus block

The patient lies flat on a horizontal operating table with a soft cushion under the shoulder on the surgical side. A high-frequency linear array ultrasound probe is used, which is placed parallel to the inferior border of the clavicle on the affected side. The patient's head is turned to the non-surgical side, and the affected limb can be moderately abducted to obtain the best view of the subclavian costoclavicular space. The ideal ultrasound view is that the three bundles of the brachial plexus are arranged sequentially on the lateral aspect of the axillary artery, however, the patient is not forced to move the affected limb given that the patient is unable to move the affected limb due to pain. After adjusting the direction and position of the ultrasound probe to obtain the best view, the anesthesia practitioner disinfects the proposed puncture site and implements the subsequent operation with strict aseptic measures. Use a 30 ml syringe containing 30 ml of 0.5% ropivacaine prepared before anesthesia. The puncture point is anesthetized with 2-3 ml of 1% lidocaine for skin infiltration. Using the in-plane technique, the nerve stimulation needle is injected from lateral to medial, posterior bundle injection of an equal dose of local anesthetic.

All patients received ultrasound-guided superficial cervical plexus block to supplement shoulder analgesia with about 10ml of 0.5% ropivacaine.

###### Local anesthetic dose allocation based on body weight

We set the initial capacity to 0.45ml/kg. According to the upper and lower sequential method, the volume varies by 0.05 ml/kg in increments or decreases, determined by the response of the previous subject. If the postoperative pain score of the previous subject ≤ 3 points, it is defined as a successful block and volume reduction in the next subject. If the postoperative pain score of the previous subject is > 3 points, it is defined as block failure and volume increase for the next subject.

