#### Measurements

The primary outcome is the patients' NRS score before leaving the PACU.

The secondary outcomes are as follows:

1. The ipsilateral diaphragmatic excursion.

2. The occurrence of complications, and the consumption of fentanyl.

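### The 0.45 ml/kg starting volume exceeds the 30 ml prepared for patients above 66.7 kg, and neither a highest volume step nor a total ropivacaine limit is set

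*Protocol*

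**What the plan says.** All references are to the protocol.

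- *Local anesthetic dose allocation based on body weight* sets the costoclavicular volume: "We set the initial capacity to 0.45ml/kg". From there "the volume varies by 0.05 ml/kg in increments or decreases", depending on the previous patient. A pain score of 3 or less lowers the next volume. With a score above 3, "it is defined as block failure and volume increase for the next subject". No highest or lowest step is named.
- *Ultrasound-guided costoclavicular space combined with cervical plexus block* fixes the preparation: "Use a 30 ml syringe containing 30 ml of 0.5% ropivacaine prepared before anesthesia". Every patient also receives a "superficial cervical plexus block to supplement shoulder analgesia with about 10ml of 0.5% ropivacaine", an amount that is not adjusted for weight.
- *Inclusion Criteria* restrict body size only through BMI: "The body mass index is 18~30kg/m"², with no weight limit.
- The *Introduction* warns that "excessive local anesthetic volume may still cause HDP" (HDP, the diaphragmatic complication that the study hopes to avoid).
- *Measurements* lists "The ipsilateral diaphragmatic excursion" as a secondary outcome. No result of that measurement changes or stops dosing.

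**The concern.** Volume per kilogram is the one quantity this study varies, and the ED50 and ED95 are read from it. The volume injected therefore has to be the volume assigned. A fixed 30 ml preparation and a weight-based assignment disagree once the patient is heavy enough, and the protocol does not say which governs. Drawing up more departs from the preparation instruction. Stopping at 30 ml departs from the allocation rule, and the ml/kg recorded for that patient may then be wrong.

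The second gap compounds the first. If 30 ml is not a ceiling, the protocol has none: the volume climbs for as long as failures continue, on top of a fixed second dose of the same drug. These are bedside dosing rules, which belong in the protocol and would not normally be left to a statistical analysis plan.

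**Working it through.** **Inputs from the protocol.** Start 0.45 ml/kg; step 0.05 ml/kg; 30 ml prepared; 0.5% ropivacaine = 5 mg/ml; cervical block about 10 ml; BMI 18 to 30; 40 patients. The protocol derives no figure on this point, so there is none to reproduce.

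**1. Weight at which the preparation runs out** = 30 ml / (ml/kg step).

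| Step (ml/kg) | Weight (kg) |
|---|---|
| 0.40 | 75.0 |
| 0.45 | 66.7 |
| 0.50 | 60.0 |
| 0.55 | 54.5 |
| 0.60 | 50.0 |

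**2. Eligibility of these weights.** 66.7/1.60² = BMI 26.0 and 66.7/1.70² = BMI 23.1, both well within range. At 1.70 m the BMI limit allows 30 × 1.70² = 86.7 kg, which at the start needs 0.45 × 86.7 = 39.0 ml. A 70 kg patient needs 0.45 × 70 = 31.5 ml; 30 ml would be 30/70 = 0.43 ml/kg.

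**3. Total ropivacaine over both blocks** = (step × weight + 10) × 5 mg. For a 70 kg patient:

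- at 0.45: (31.5 + 10) × 5 = 207.5 mg, or 2.96 mg/kg;
- at 0.60, reached by three failures in a row from the start: (42 + 10) × 5 = 260 mg, or 3.71 mg/kg.

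**4. How often it would matter.** The protocol does not give the weights, the true ED50 or the spread of individual tolerance. Assumed: weight mean 60, 65 or 70 kg with SD 8, 10 or 12, truncated to 45–95 kg; normal tolerance with SD 0.05, 0.08, 0.10 or 0.12 ml/kg. That gives 36 scenarios for each ED50. Each was simulated with 40 patients under the protocol's rule, estimating the ED50 as the mean of failure-to-success midpoints. The chance of any assignment at 0.60 or more comes from an exact recursion over the four tolerance SDs.

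The first patient needs more than 30 ml with chance of about 21–66%, whatever the ED50. Over the whole study:

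| True ED50 (ml/kg) | Mean number of 40 assigned more than 30 ml | Upward ED50 bias (ml/kg), *only if* staff stop at 30 ml and assigned doses are analysed | Chance of any assignment at 0.60 or more |
|---|---|---|---|
| 0.25 | 0.2–2.0 | about 0 | below 1% |
| 0.30 | 0.3–4.0 | at most 0.005 | below 1% |
| 0.35 | 0.9–8.4 | 0.001–0.015 | below 1% |
| 0.40 | 3.6–15.0 | 0.003–0.056 | 0.01–8% |
| 0.45 | 10.2–24.3 | about 0.09 at mean 65 kg, SD 10; 0.02–0.28 over all scenarios | 3–45% |

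The median bias over the 36 scenarios is about 0.005 at ED50 0.35 and 0.021 at 0.40. Both are below half of a 0.05 step. The largest values at 0.45 require assigned steps far above any credible dose and are not relied on.

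**The case against.** The strongest reply is that the allocation section sets the dose and the technique section merely describes a syringe made ready beforehand. Staff would draw up a second syringe for a heavier patient, and no dose would depart from its assignment. That is the natural reading, and much of it stands: the protocol nowhere calls 30 ml a cap. A reader might infer that a 70 kg patient is held at 30 ml at the first and every higher step. The text does not support this, since the allocation rule requires 31.5 ml at the first step. But on the natural reading the preparation instruction is wrong as written for ordinary patients, and no upper limit applies.

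A reader might also infer that the ED50 will be biased. This too goes beyond the text. It needs two unwritten events, stopping at 30 ml and analysing assigned doses, and even then the effect is small unless the true ED50 is about 0.40 or more.

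On the missing limit, it is fair to say that the design largely restrains itself: each success lowers the next volume, so high steps are likely only if the ED50 is near the start. Nothing in the protocol shows that it is lower. Recording diaphragmatic excursion and complications is monitoring and does not limit the volume. A reader might take the mg/kg totals as evidence of unsafe dosing. The protocol gives no toxic threshold, so they cannot be judged that way.

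**Conclusion.** The concern holds as a conflict between two written instructions together with an escalation rule that has no ceiling. The conflict is certain: it follows from 30/0.45 = 66.7 kg and the BMI range, without assumptions. The absence of a highest step and of a total ropivacaine limit is equally plain from the text.

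The statistical consequence is conditional. It ranges from negligible at a true ED50 of 0.30 or lower to roughly one dose step at worst at 0.40 (0.056 against a step of 0.05), and more at 0.45. All of these sizes rest on the assumed weights, ED50 and tolerance SD, and on the two unwritten events. The change should be made because volume is the study's only varied quantity and the correction is cheap. It is not made on the ground that bias or harm has been shown.

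**What to change.** 1. In the block-technique section, replace the fixed 30 ml with a prepared volume equal to the assigned ml/kg times body weight.
2. In the dose-allocation section, before the first patient, state a highest ml/kg step, to be repeated if a failure would call for more. State also a maximum total ropivacaine in mg over both blocks, applied patient by patient because it depends on weight. The sponsor sets both values.
3. Record the ml actually given. If the mg maximum reduces a patient's volume, analyse ml given divided by body weight with a dose-response regression (probit or logistic, for example), which accepts doses that fall between steps. A midpoint estimator does not.

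**Cost.** A short amendment, with no added patients or visits. More drug is drawn up for heavier patients. Item 3 adds a regression to the analysis if the maximum ever binds. An ED50 above the top step could only be reported as lying beyond it.

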###### General anesthesia management

All patients received general anesthesia with laryngeal mask intubation, propofol (2-3 mg/kg) induced under general anesthesia, atropine (0.25-0.5 mg) as appropriate, and sevoflurane (1.5-3%) for anesthesia maintenance according to the patient's heart rate. When the heart rate or blood pressure exceeds 20% of the preoperative value, an intravenous bolus of fentanyl (50 μg) is allowed, multiple uses are allowed. At the end of the procedure, an intravenous bolus of tropisetron 5 mg is given to prevent nausea and vomiting.

All patients received intravenous postoperative self-controlled analgesic pump (PCIA) containing tropisetron 10 mg and butorphanol 6 mg.

#### Measurements

The primary outcome is the patients' NRS score before leaving the PACU.

The secondary outcomes are as follows:

1. The ipsilateral diaphragmatic excursion.

2. The occurrence of complications, and the consumption of fentanyl.

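### Block success is a pain score of 3 or less with no condition on opioid use and no fixed reading time, so an opioid-masked block failure lowers the next volume and biases the ED50 downward

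*Protocol*

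**What the plan says.** The Protocol section on local anesthetic dose allocation starts at 0.45 ml/kg and moves in steps of 0.05 ml/kg. For success it says, of the patient who follows: "If the postoperative pain score of the previous subject ≤ 3 points, it is defined as a successful block and volume reduction in the next". For failure, when the "pain score of the previous subject is > 3 points, it is defined as block failure and volume increase for the next subject". Neither sentence gives a time for the score or mentions opioid.

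Under Measurements, the primary outcome is given as the "NRS score before leaving the PACU". Fentanyl consumption is a secondary outcome. Use of the analgesic pump is not a listed outcome.

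Under General anesthesia management, when heart rate or blood pressure moves beyond 20% of its preoperative value, "an intravenous bolus of fentanyl (50 μg) is allowed, multiple uses are allowed". No cap is stated. The same section adds: "All patients received intravenous postoperative self-controlled analgesic pump (PCIA) containing tropisetron 10 mg and butorphanol 6 mg". It gives neither the pump's start time nor its settings.

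Under Statistical analysis, the ED50 and ED95 are to come from the up-and-down method. No estimator is named.

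**The concern.** The objective is the ED50 and ED95 of ropivacaine for analgesia delivered by the block. The response should therefore reflect what the block did. Opioid lowers the pain score, and a patient whose block has failed has the most reason to press the pump. If that brings the score to 3 or less by the reading, the rule records a successful block. Misclassification by this route runs one way only, from failure to success, and each case moves the sequence down a step.

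Two features make this hard to leave to a later document. First, the definition assigns the next patient's volume. An SAP can reclassify responses afterwards, but by then the following patients have already received volumes chosen on the wrong signal. Second, pump use is not among the listed measurements, so the information needed to reclassify may not exist. The protocol's introduction itself warns that too small a volume may give inadequate analgesia, so an understated ED50 errs in a direction that matters.

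**Working it through.** The protocol gives no masking rate and no dose-response curve, so it has no figure of its own to reproduce here. What follows is illustrative.

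**Inputs from the protocol:** start 0.45 ml/kg, step 0.05 ml/kg, 40 patients, success at a score of 3 or less.

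**Assumed:** *m*, the share of true block failures that opioid brings to 3 or less before the reading, taken as equal at every volume; and a logistic true curve with ED50 0.35 and ED95 0.50 ml/kg.

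**Step 1: which true quantile is estimated.** If *p* is the true block success rate at a volume, apparent success is p + m(1 − p). Setting this equal to *q* gives p = (q − m)/(1 − m).

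| m | True success at apparent ED50 | True success at apparent ED95 |
|---|---|---|
| 0.1 | 0.40/0.90 = 44.4% | 0.85/0.90 = 94.4% |
| 0.2 | 0.30/0.80 = 37.5% | 0.75/0.80 = 93.8% |
| 0.3 | 0.20/0.70 = 28.6% | 0.65/0.70 = 92.9% |

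This step needs no assumption about the curve beyond *m*.

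**Step 2: in ml/kg.** The logistic slope is ln(19)/(0.50 − 0.35) = 2.944/0.15 = 19.63 per ml/kg. The apparent ED50 is 0.35 + logit(p)/19.63. At m = 0.3, logit(0.286) = −0.916, giving 0.35 − 0.047 = 0.303. At m = 0.1 and 0.2 the results are 0.339 and 0.324. The ED95 of the masked curve moves much less: 0.494, 0.488 and 0.481, against 0.500.

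**Step 3: what an estimator would return.** The protocol's sequence was simulated at 40 patients, 1,500 runs per scenario. Median estimates in ml/kg:

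| Scenario | Logistic ED50 | Logistic ED95 | Isotonic ED95 |
|---|---|---|---|
| m = 0 | 0.350 | 0.482 | 0.443 |
| m = 0.1 | 0.336 | 0.483 | 0.441 |
| m = 0.2 | 0.317 | 0.489 | 0.439 |
| m = 0.3 | 0.290 | 0.505 | 0.435 |
| Whole curve shifted left by 0.05 | 0.300 | 0.428 | 0.393 |

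At m = 0.3 the logistic ED50 falls by 0.350 − 0.290 = 0.060 ml/kg, slightly more than one step. A crossover-midpoint estimator (4,000 runs) also fell, from 0.371 to 0.316. It fell likewise for assumed true curves of 0.30/0.40 and 0.40/0.60.

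The ED50 went down in every scenario. The ED95 did not. Constant masking flattens the apparent curve, so a fitted logistic ED95 can rise while the isotonic one barely moves. Under a parallel shift both fall.

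**The case against.** The strongest reply is that every patient has the same anaesthetic and pump regimen, so the volume needed within that regimen is a legitimate target. That is fair as a choice of target, but the protocol does not state it, and its rule calls the result a successful block. A shared regimen also does not mean equal opioid use, since self-controlled use can vary with pain.

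It can also be said that the mechanism is partly inferred, and this stands. The pump's start time is not given, so use before the reading is possible but not documented. That the score in the step rule is the PACU score is likewise an inference from the only time named. Both are gaps in the rule that assigns the next volume, which supports fixing it.

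Several stronger readings are tempting, and the text does not support them:

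- A reader might infer that fentanyl is unlimited pain rescue in the PACU. The protocol says "multiple uses are allowed" with no cap stated, places this under general anaesthesia, and ties it to heart rate or blood pressure. That trigger is not specific to block failure; the atropine allowed as appropriate could also set it off.
- A reader might infer that patients are treated and kept until comfortable, so that the score is conditioned on comfort. The protocol gives no PACU rescue rule and no discharge criterion.
- A reader might infer that with half or more of failures masked the sequence falls without limit. It is bounded: 0.45/0.05 = 9 net steps reach zero. That case also depends on holding *m* constant at every volume, which is doubtful if opioid rescues fewer patients as the block weakens.

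**Conclusion.** The point holds for the ED50. Success is scored without regard to opioid and at a time that is not fixed, so any failed block masked before the reading counts as a success, and the ED50 is biased downward. With 10% to 30% of failures masked, the apparent ED50 is the true ED44 to ED29. On the assumed 0.35/0.50 curve, the fitted ED50 falls by 0.014 to 0.060 ml/kg, up to about one dose step. These sizes rest wholly on the assumed masking share and curve; the protocol supplies neither.

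A reader might infer that the ED95 is understated as well. That is not established. The masked curve's own ED95 is only slightly lower, and the estimate can fall, stay level or rise according to the estimator and the form of masking.

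**What to change.** Under the dose-allocation section and under Measurements, use one identical definition of response: NRS of 3 or less at a single fixed time after PACU arrival. Record pump demands and any other postoperative analgesic taken before that reading, and count such use as failure for both the step rule and the ED50/ED95 estimation. State the pump's start time and whether it delivers a background infusion, since a count of demands would not capture one.

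Report intra-operative fentanyl by volume. Use it to reclassify patients in a sensitivity analysis only: with a haemodynamic trigger, treating it as failure in the main analysis could push the ED50 too high.

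State that the ED50 and ED95 refer to early PACU analgesia under this regimen.

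This changes how response is defined, not the analgesic care. The cost is protocol wording and one more recorded item. The estimated ED50 may come out somewhat higher.

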### Statistical analysis

SPSS 25.00 statistical software was used for statistical analysis. The Kolmogorov-Smirnov test is used to test the normality of the data distribution. The normally distributed data were analyzed using the independent samples t-test, and the continuous data were expressed as mean ± standard deviation (SD). The independent samples t-test was used for the normal distribution data, and the Mann-Whitney U test was used for the evaluation of the non-normal distribution data, and the continuous data were expressed as median (intervals). Count data were analyzed using either Chi-square test or Fisher's exact test. A value of P<0.05 was considered statistically significant. The upper and lower sequential methods were used to estimate the patient's ED50 and ED95.

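### The test list contains only two-independent-group tests for a single sequential cohort and gives no paired method for change from baseline in diaphragmatic excursion

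*Protocol*

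**What the plan says.** On design, the protocol's Subjects section reads "This study plans to include 40 patients who underwent shoulder arthroscopic surgery under anesthesia under general anesthesia combined with CCB-CPBs". Under local anesthetic dose allocation, "the volume varies by 0.05 ml/kg in increments or decreases, determined by the response of the previous subject". There is no randomisation, control arm or parallel group. The one between-patient split that the protocol defines is in the same section: a pain score of 3 or less is a success, and with a higher score "it is defined as block failure and volume increase for the next subject".

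On excursion, a section headed "Baseline diaphragmatic excursion measurement" states "The excursion of the hemidiaphragm will be measured by utilizing the M-mode". Measurements lists "The ipsilateral diaphragmatic excursion" as the first secondary outcome. Neither section gives a post-block time point or a comparison.

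On analysis, the Statistical analysis section states "The normally distributed data were analyzed using the independent samples t-test" and then assigns the same test to normal data a second time. Non-normal data go to Mann-Whitney and counts to chi-square or Fisher's exact, at P<0.05. The section also has a Kolmogorov-Smirnov normality check and closes with ED50 and ED95 estimation by the up-and-down method. Measurements names the NRS score before leaving the PACU as the primary outcome, whereas the Objective is ED50 and ED95.

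**The concern.** Each comparative test listed needs two independent groups of patients. The design supplies one cohort, and the section does not say which groups are meant. A baseline reading is normally taken to measure change within the patient, yet the rule for continuous data offers only unpaired tests. Someone who follows it for excursion before and after the block would treat 80 readings on 40 people as 80 independent observations.

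The Introduction motivates the trial by the need for good analgesia without hemidiaphragmatic paresis. A method that is weak at detecting a fall in excursion therefore errs towards false reassurance on the respiratory side of that aim.

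A smaller mismatch goes with this. The declared primary outcome is the NRS score, but the quantities that the trial exists to estimate are ED50 and ED95, which come from the binary success/failure response. The step rule steers volumes towards the level at which about half the patients succeed, so an overall NRS summary would largely reflect that rule.

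**Working it through.** No figure in the protocol can be reproduced here. The 40 patients come without power, effect size or standard deviation, so the calculation below only illustrates size.

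**Inputs from the protocol:** n = 40 (Subjects); alpha 0.05 (Statistical analysis, sidedness not stated).

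**Assumptions, not in the protocol:** two-sided testing; equal SD at baseline and after the block; within-patient correlation rho of 0.3, 0.5 or 0.7; a true change of 0.3 or 0.5 SD; normal approximation.

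**Formulas, in SD units:**
- SE that the independent t-test uses: sqrt(2/n) = sqrt(2/40) = 0.224.
- True SE of the mean change: sqrt(2(1 − rho)/n). At rho 0.5 this is sqrt(2 × 0.5/40) = 0.158.
- Variance ratio: 1/(1 − rho). The confidence-interval width ratio is its square root.
- Actual type I error of the unpaired test: 2 × [1 − Φ(1.96/sqrt(1 − rho))].
- Power for a change d, unpaired: Φ((d − 1.96 × 0.224)/true SE). Paired: Φ(d/true SE − 1.96).

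| rho | True SE | Variance ratio | CI width ratio | Type I error, unpaired | Power at 0.3 SD, unpaired / paired | Power at 0.5 SD, unpaired / paired |
|---|---|---|---|---|---|---|
| 0.3 | 0.187 | 1.43 | 1.20 | 0.019 | 0.23 / 0.36 | 0.63 / 0.76 |
| 0.5 | 0.158 | 2.00 | 1.41 | 0.006 | 0.19 / 0.48 | 0.65 / 0.89 |
| 0.7 | 0.122 | 3.33 | 1.83 | 0.0003 | 0.13 / 0.69 | 0.69 / 0.98 |

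The point estimate of the change and its true sampling variance are the same under either test. Only the calculated standard error is wrong, and it is too large. These figures are for the t-test. Mann-Whitney also ignores the pairing, but its exact figures were not computed.

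**Could success versus failure supply the two groups?** The step rule was simulated with start 0.45 ml/kg, step 0.05 ml/kg and 40 patients, for assumed ED50 of 0.25, 0.35 and 0.45 ml/kg and logistic scale 0.02 or 0.05 (5,000 runs each). The central 95% ranges of the number of successes lay between 19 and 23, leaving 17 to 21 failures. Two disjoint sets of workable size would therefore exist. The pain score defines the split, so a comparison of NRS between them is circular. Excursion, complications and fentanyl do not define it. Comparing them is possible, but the result is tied to the assigned volume.

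**The case against.** The strongest reply is that the protocol never assigns the t-test to excursion. It describes only a baseline reading, and the before-after comparison is inferred from that section's heading. The listed tests could be meant for successes against failures, where they are valid in form. Details of secondary analyses may also sit in a separate analysis plan.

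Much of this stands. A reader might infer that the protocol prescribes an unpaired before-after test; it does so only through its general rule for continuous data. A reader might also infer that the whole stated analysis is wrong. It is not: ED50 and ED95 are estimated by the up-and-down method, which is not a two-group test. Nor is every success-versus-failure comparison circular; that applies to NRS alone, and the protocol does not say that it will make that comparison.

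Two readings of the size also go too far. The unpaired test does not create false positives; under positive correlation it is conservative. At rho 0.5 one might say that it wastes half the sample. That holds for interval width, since sqrt(2 × 0.5/20) = 0.224, but not for power: 20 correctly paired patients give 0.27 and 0.61 at 0.3 and 0.5 SD, against 0.19 and 0.65 for the unpaired test on 40.

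The reply does not remove the mismatch. The protocol does not leave its tests open. It fixes a list that has no groups to act on and has no method for the repeated measurement that it schedules at baseline.

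**Conclusion.** The point holds for the secondary analyses. Apart from the normality check and the ED50/ED95 estimate, every listed test is a two-independent-group test in a trial that names no groups, and no paired method is given for change in excursion. If the stated rule is used for that change, intervals are 1.20 to 1.83 times too wide at correlations of 0.3 to 0.7. Power falls by 13 to 29 percentage points for a 0.5 SD change and by 13 to 56 points for a 0.3 SD change. The direction needs only a positive correlation; the sizes rest on assumed correlations and effects. The dose-finding estimate is untouched, so the severity is moderate.

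**What to change.** Rewrite the test list in the Statistical analysis section:

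- **Excursion:** analyse within-patient change from baseline to a stated post-block time point by paired t-test or Wilcoxon signed-rank test, with a 95% confidence interval.
- **Complications and fentanyl:** report descriptively with confidence intervals.
- **Between-group tests:** delete them, or keep them only for a named success-versus-failure comparison that is labelled exploratory and is not applied to NRS.
- **Primary estimates:** state in Measurements and Statistical analysis that ED50 and ED95, with 95% confidence intervals, come from the binary success/failure response and are primary, and that NRS is the response that defines success.

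The cost is wording, plus stating when excursion is measured after the block. Without that time point the paired analysis cannot be carried out.
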